## Objectives

To address the lack of studies in the asymptomatic hyperuricemia population, we will investigate the efficacy and safety of acupuncture on SUA levels in adults with asymptomatic hyperuricemia, and, if found, whether or not the effect of acupuncture on SUA levels can last for at least 12 weeks. This study will be the first to use non-penetrating sham acupuncture for the control group. The de qi sensation from acupuncture will be quantified to investigate the specific effect of acupuncture on SUA levels in this clinical population.

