## Outcomes

### Primary outcome

Participants’ SUA levels will be evaluated at six time points during the study: once at baseline (week 0), twice during the treatment period (4 and 8 weeks post randomization), and three times during the follow-up period (12, 16, and 20 weeks post randomization). The primary end point of this study is the reduction in SUA level from baseline to 8 weeks after randomization.

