### Secondary efficacy outcomes

The reduction in SUA level at 4, 12, 16, and 20 weeks after randomization will also be evaluated. Additional secondary outcomes comprise the proportion of participants with SUA ≤ 6.0 mg/dL, the proportion of participants with SUA ≤ 7.0 mg/dL, the proportion of participants with gout attacks post randomization, body weight, and the amount of acute medication taken. These outcomes will be recorded at baseline (week 0), during the treatment period (4 and 8 weeks post randomization), and during the follow-up period (12, 16, and 20 weeks post randomization).

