#### Statistical analysis

Statistical analyses will be performed using SAS (SAS Institute, v.9.4) by an independent statistician who is blinded to group allocation. Efficacy analyses will be performed primarily on the full analysis set (FAS). A sensitivity analysis will be performed on the per-protocol set (PPS) if deemed necessary.

The primary end point will be summarized descriptively, and the hypothesis will be tested based on the analysis of covariance (ANCOVA) model with the intervention group as the main effect and baseline SUA and study center as covariables.

For other end points, continuous data yielding normal distributions will be summarized using means and standard deviations. Differences between the two groups will be tested using Student’s *t*-test. For results with non-normal distributions, data will be expressed using medians and quartiles, and comparisons between the two groups will be performed using the Mann–Whitney *U* test. Categorical end points will be summarized in terms of frequencies and percentages, and comparisons between the two groups will be performed using the Pearson *χ*² test or Fisher’s exact test, as appropriate. The statistical test for the primary end point will be at the one-sided 0.025 alpha level. Unless otherwise specified, all other end points will be tested at the two-sided 0.05 alpha level.

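### SUA reduction at weeks 4, 12, 16 and 20 loses the baseline and center adjustment used at week 8, although durability of the effect is a stated objective

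*Protocol article*

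**What the plan says.** The Primary outcome section states: "The primary end point of this study is the reduction in SUA level from baseline to 8 weeks after randomization". The Statistical analysis section tests this with an "analysis of covariance (ANCOVA) model with the intervention group as the main effect and baseline SUA and study center as covariables".

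The rest are handled by a general rule in the same section: "For other end points, continuous data yielding normal distributions will be summarized using means and standard deviations". The next sentence reads "Differences between the two groups will be tested using Student’s *t*-test". For non-normal data, medians and quartiles are given and "comparisons between the two groups will be performed using the Mann–Whitney *U* test". Neither test carries a covariate. The phrase about exceptions at the end of that section concerns only the alpha level, and no other section gives these end points an adjusted or repeated-measures model.

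Secondary efficacy outcomes places the other SUA visits under that rule: "The reduction in SUA level at 4, 12, 16, and 20 weeks after randomization will also be evaluated". Body weight is listed there too. The Objectives section asks, of the effect on SUA, "if found, whether or not the effect of acupuncture on SUA levels can last for at least 12 weeks". The Discussion places those 12 weeks after the end of treatment. Under Randomization and blinding, allocation is stratified by study center.

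On timing, Secondary efficacy outcomes says of the additional outcomes, body weight among them: "These outcomes will be recorded at baseline (week 0". Table 1 marks weight at week −4 and not at week 0.

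**The concern.** The same measurement in the same participants is estimated by one method at week 8 and by another at the visits before and after it. The durability question is a comparison along that series, so the method should stay constant across it. A normality check at each visit adds a second break: one visit could report a difference in means and the next a comparison of ranks with medians, and the two cannot be read as one trajectory.

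Baseline SUA and center are already collected and already in the primary model, so leaving them out saves nothing. What is at stake is the precision and readability of the follow-up results, where an effect may be smaller than at week 8. The primary conclusion is not affected. The protocol itself fixes these tests, so this is not a detail left to an unseen analysis plan.

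**Working it through.** **Inputs from the Sample size section:** difference 0.58 mg/dL, SD 1.15 mg/dL, one-sided alpha 0.025, power 85%, 71 per group, 20% attrition.

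**Inputs not in the protocol (assumed):** correlation ρ between baseline and follow-up SUA, taken as 0.3 to 0.9; equal SD σ at both times; 1.15 read as the SD of the change; and the planned effect applied to a secondary visit.

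**1. The plan's own figure.** n per arm = 2(1.960 + 1.036)² × (1.15/0.58)² = 2 × 8.978 × 3.931 = 70.6, so 71 per arm and 142 in total. The noncentral t gives 72 per arm, which is close enough. With 20% attrition, 142/0.8 = 177.5, so 178 against 180 planned. The sample size reproduces and is not in dispute.

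**2. Power of the planned t-test on reduction, 71 per arm.** SE = 1.15 × √(2/71) = 0.193. Then 0.58/0.193 = 3.005, and Φ(3.005 − 1.960) = 85.2%. Two-sided 0.05 has the same critical value for a favorable effect.

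**3. ANCOVA against the t-test on change.** Var(change) = 2σ²(1 − ρ). The ANCOVA residual variance is σ²(1 − ρ²). The ratio is (1 + ρ)/2.

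| ρ | Variance ratio | Variance cut | ANCOVA power | Gain over 85.2% (points) | n per arm for 85% |
|---|---|---|---|---|---|
| 0.3 | 0.65 | 35% | 96.1% | 10.9 | 46 |
| 0.5 | 0.75 | 25% | 93.4% | 8.2 | 53 |
| 0.7 | 0.85 | 15% | 90.3% | 5.1 | 61 |
| 0.9 | 0.95 | 5% | 86.9% | 1.7 | 68 |

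**4. A second set of assumptions.** The eligibility window of 7–11 mg/dL may make the baseline SD smaller than the follow-up SD. Take follow-up SD 1.15 and baseline SD 0.8 to 1.15. Solving SD(change)² = s₀² + s₁² − 2ρs₀s₁ gives ρ of 0.35 to 0.50 and a variance cut of 12% to 25%. With 72 per arm, power at 0.58 mg/dL is 85% for the t-test and 89–93% for ANCOVA. At a faded effect of 0.40 mg/dL it is 54% and 60–67%.

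**5. Chance baseline imbalance.** Under equal variances, a baseline difference d shifts the unadjusted change-score comparison by (1 − ρ)d in absolute size. One standard error of d is σ√(2/71).
- ρ = 0.5: σ = 1.15, d = 0.193, shift = 0.097 mg/dL, or 17% of 0.58.
- ρ = 0.7: σ = 1.48, d = 0.249, shift = 0.075 mg/dL, or 13% of 0.58.

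**6. Body weight.** It is listed as a level, not as a change. If raw levels are compared, baseline is not used at all, and baseline adjustment would multiply the residual variance by 1 − ρ². At an assumed ρ of 0.9 that is 1 − 0.81 = 0.19. The loss from an unadjusted test of level therefore grows with ρ, the opposite of the pattern in step 3.

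**The case against.** The strongest reply is that the planned test is sound. The secondary SUA outcomes are defined as reductions, so the t-test already subtracts each participant's baseline. Under randomization it is unbiased and targets the same mean difference as the week-8 ANCOVA. These are secondary outcomes, the gain is small if ρ is high, and ρ is unknown. All of this stands. It limits the point to precision, residual imbalance, the missing center term and consistency across visits.

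Three stronger readings are tempting, and the protocol does not support them.

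- A reader might infer that baseline SUA is discarded and the follow-up results are biased. The definition as a reduction rules that out.
- A reader might infer an inflated false-positive rate for durability. Three follow-up tests at two-sided 0.05, with assumed correlations of 0.4 to 0.8, give a 10–13% chance of at least one false positive in either direction. But an effect lasting at least 12 weeks after treatment ends at week 8 points to week 8 + 12 = 20, which is one test. Nothing in the protocol lets any one significant visit establish durability, and the Objectives section already makes the question conditional on an effect being found.
- A reader might infer that an effect could seem to appear or vanish purely because the method changed. The critical value for a favorable effect is the same at every visit, and the differences in power are modest.

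The reply does not defend letting observed normality choose the test, or leaving out a stratification factor that the primary model includes.

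**Conclusion.** The point holds as one of efficiency and consistency in the secondary analyses. The protocol fixes a less precise and data-dependent method for SUA at weeks 4, 12, 16 and 20, although persistence of the effect is part of its objective. Under equal variances and ρ from 0.3 to 0.9, the unused variance reduction is about 35% to 5%, or about 11 to 2 points of power at 0.58 mg/dL with 71 per arm. The range rests wholly on an assumed ρ and on applying the week-8 effect to later visits. The cost of omitting center cannot be sized from the protocol. The planned t-test remains valid.

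For body weight, the same adjustment is advisable. Separately, Table 1 and Secondary efficacy outcomes disagree on when its baseline is taken, with four weeks of lifestyle guidance that includes weight control lying between the two dates.

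**What to change.** - Analyze SUA reduction at every visit with the primary model's terms (group, baseline SUA, center), either by visit-wise ANCOVA or by one repeated-measures model that adds visit and group-by-visit.
- Report adjusted mean differences with 95% CIs whatever a normality check shows, and keep Mann–Whitney as a sensitivity analysis only.
- State that the claim of an effect lasting at least 12 weeks is read from week 20.
- Analyze body weight by ANCOVA with its recorded baseline and center, and reconcile Table 1 (week −4) with Secondary efficacy outcomes (week 0).

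The SUA changes are wording in the statistical section. They need no added patients or measurements and should be settled before unblinding. The weight baseline is less simple. The Discussion says that recruitment began on 13 July 2022 and data collection is well underway, so a week-0 weight that was not taken cannot be recovered for participants already randomized. Adding one now would mix two baseline dates and require an amendment to go to the ethics committee. The practical course is to establish which weight was actually recorded, use it, and correct whichever passage is wrong.

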### Inclusion criteria

Meets the diagnostic criteria for hyperuricemia, in accordance with the guidelines of the American College of Rheumatology (2012) (37).Aged 18–65 years (regardless of sex),SUA ≥ 7–11.0 mg/dL after 1 month of a low-purine diet,No history of gouty arthritis.Has not received uric acid-lowering drug treatment or stopped uric acid-lowering drug treatment ≥ 12 weeks before randomization.18.5kg/m^2^ ≤ body mass index (BMI) ≤ 30.0 kg/m^2^.Written informed consent.

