### Randomization and blinding

The Clinical Research Center affiliated to the Tongji Hospital of HUST are responsible for the design of the randomization protocol for this study. After confirmation of eligibility, participants will be randomly allocated to either the verum acupuncture or sham acupuncture group in a 1:1 ratio. Participants will be stratified according to study center, and a permuted block randomization method with a block size of four will be used. The randomization sequences will be computer-generated using a central randomization system and according to the order of participant enrollment. Each research center will have an independent research assistant responsible for generating allocation sequences through a password-protected central randomization system. Acupuncturists will be made aware of group assignments prior to treatment using opaque, sealed envelopes.

As this is a blinded study, participants, outcome assessors, and statisticians will be blinded to treatment assignment. To maintain blinding in participants, acupuncturists will perform a standardized acupuncture ritual across both groups. Because acupuncturists perform acupuncture through the manipulation of needles, the masking of acupuncturists is difficult to achieve.

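### The SUA ≤ 7.0 mg/dL response is to be compared without adjustment for baseline SUA, which is valid but gives up precision that the primary model already keeps

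*Protocol article*

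**What the plan says.** The article, under *Secondary efficacy outcomes*, lists two response outcomes based on absolute thresholds: "the proportion of participants with SUA ≤ 6.0 mg/dL, the proportion of participants with SUA ≤ 7.0 mg/dL". They are recorded at week 0 and at weeks 4, 8, 12, 16 and 20. No minimum fall from baseline is required.

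Under *Inclusion criteria*, patients must have "SUA ≥ 7–11.0 mg/dL after 1 month of a low-purine diet", which I read as 7 to 11.0 mg/dL inclusive.

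Under *Statistical analysis*, the test for these outcomes is fixed: "Categorical end points will be summarized in terms of frequencies and percentages, and comparisons between the two groups will be performed using the Pearson" chi-square or Fisher's exact test, at the two-sided 0.05 level. The same section gives the primary end point an ANCOVA "with the intervention group as the main effect and baseline SUA and study center as covariables". Under *Randomization and blinding*: "Participants will be stratified according to study center, and a permuted block randomization method with a block size of four will be used".

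**The concern.** The response outcomes dichotomise the same laboratory value as the primary end point but drop both covariates. Baseline matters more here than for the primary. A change score has already subtracted the starting value, whereas an absolute threshold has not. A patient entering at 7.2 mg/dL needs a fall of 0.2 to respond; one entering at 10 needs a fall of 3.0.

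At stake are the precision of the estimated difference in response, the power of a secondary comparison that is already modest, and agreement with the primary model. If the arms differ by chance in baseline SUA, the ANCOVA corrects for it and the response comparison does not, so the two results could diverge for that reason alone.

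**Working it through.** **1. The plan's own figure.** Inputs from *Sample size*: difference 0.58 mg/dL, SD 1.15, one-sided alpha 0.025, power 85%, attrition 20%.

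n per arm = 2 × (1.960 + 1.036)² × 1.15² / 0.58² = 2 × 8.98 × 3.931 ≈ 70.6, rounded up to 71, so 142 in total. Then 142 / 0.8 = 177.5, so 178, and 180 suffices. The stated figure is reproduced. The article gives no power for the response outcomes.

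**2. How strongly response depends on baseline.** With baseline *b*, cut-off *c*, no mean change and SD of change 1.15, P(response) = Φ((c − b)/1.15):

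| Baseline (mg/dL) | P(SUA ≤ 7.0) | P(SUA ≤ 6.0) |
|---|---|---|
| 7.0 | 50% | 19% |
| 7.5 | 33% | 10% |
| 8.0 | 19% | 4% |
| 9.0 | 4% | 0.5% |
| 10.0 | 0.5% | 0% |

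For example, at *b* = 8.0 and *c* = 7.0: Φ(−1/1.15) = Φ(−0.87) = 0.19.

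**3. Power and type I error for SUA ≤ 7.0.** Simulation of 142 patients in three centres, 1:1 within centre, 1,500 runs per scenario, two-sided 0.05, effect 0.58 and SD 1.15 from the article. Assumed, because the article is silent: baseline normal with the mean and SD shown, truncated to 7–11; mean sham fall 0.2 mg/dL; slope of change on baseline 0 or −0.3; no centre effect. The adjusted test is a logistic likelihood-ratio test with baseline SUA and centre.

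| Baseline; slope | Response, verum vs sham | Power, chi-square | Power, adjusted | Type I, chi-square | Type I, adjusted |
|---|---|---|---|---|---|
| N(8.0, 0.8); 0 | 39.0% vs 23.6% | 50.2% | 57.7% | 6.1% | 5.9% |
| N(8.0, 0.8); −0.3 | 38.0% vs 22.0% | 55.7% | 60.7% | 6.1% | 5.9% |
| N(8.5, 1.0); 0 | 28.1% vs 16.2% | 40.7% | 48.6% | 4.3% | 6.0% |
| N(8.5, 1.0); −0.3 | 25.9% vs 13.6% | 45.6% | 50.5% | 4.9% | 6.3% |

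The gain is 5 to 8 points. With 1,500 runs the standard error of a 5% rate is √(0.05 × 0.95/1500) = 0.56 points, so the adjusted test may run slightly above its level and a small part of the gain may come from that. A second simulation on the same two baseline assumptions, adjusting for baseline SUA only, gave 42–57% unadjusted and 48–60% adjusted, with type I error of 5.1–5.9% for SUA ≤ 7.0. Adjustment reduced the SD of the risk difference by about 3–10%.

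**4. Chance imbalance.** Under the same assumptions, a 0.2 mg/dL baseline gap between arms moves the SUA ≤ 7.0 difference by about 2–5 percentage points, against an expected treatment difference of 12–16 points (from the table, 11.9 to 16.0). With 71 per arm, a gap at least that large arises in about 8–16% of trials.

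**5. SUA ≤ 6.0.** In the four scenarios of step 3, sham response is 3–7% and verum response 8–15%. Chi-square has power 24–35% and type I error 3.9–6.0%. The adjusted likelihood-ratio test shows 30–39% power, but its type I error is 6.4–9.2% (6.3–8.0% when adjusting for baseline only), so the apparent gain cannot be relied on. In a separate simulation with a differently shaped baseline (72 per arm, response 5.4% vs 13.7%), a Wald test from ordinary logistic regression had 34.6% power against 41.4% for chi-square. Its listed inputs are incomplete, so I take only the direction from it.

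**6. Centre.** With no centre effect, a Cochran–Mantel–Haenszel test by centre gives 40–55% for SUA ≤ 7.0 against 41–56% for chi-square. With assumed centre shifts of 0, ±0.3 and ±0.6 mg/dL (144 patients, 8,000 runs), chi-square against Cochran–Mantel–Haenszel gives 51.5% vs 50.5%, 50.5% vs 50.6% and 46.6% vs 48.8%, with chi-square type I error 4.0–5.0%.

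**The case against.** The strongest reply is that nothing here is invalid. After 1:1 randomisation, Pearson and Fisher tests are proper tests of a difference in proportions. Chance baseline imbalance is already part of their sampling error, and efficacy rests on an ANCOVA that does adjust. That stands: the point is about efficiency and consistency in a secondary outcome.

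A reader might go further in four ways that the article and the calculations do not support.

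- *The standard error is materially wrong because randomisation was stratified by centre.* Step 6 shows otherwise. Even with centres spread over 1.2 mg/dL, stratifying gains about 2 points of power, and any excess in the unstratified standard error is conservative.
- *Baseline imbalance biases the comparison.* It adds noise in either direction and does not favour an arm systematically.
- *The 7.0 cut-off credits patients who never changed.* The literal overlap between entry and response is the single value 7.0. Under one assumed baseline distribution 0.16% of patients start below 7.05, or 0.0016 × 144 ≈ 0.2 patients; another could give one or two. It affects both arms alike, and the outcome is also recorded at week 0, so such patients would be visible. Moving the cut-off to below 7.0 would not deal with someone entering at 7.1.
- *Both responses should be adjusted.* Step 5 shows no dependable benefit for SUA ≤ 6.0.

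An analysis plan that is not shown might add an adjusted analysis. The article nevertheless names the test for every categorical outcome, so this is a stated choice and not a detail left open.

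**Conclusion.** The point holds for SUA ≤ 7.0 as a modest loss of efficiency. Power is about 41–57% with the planned test and 48–61% with adjustment for baseline SUA, with or without centre. Most of the gain comes from baseline SUA. These ranges rest on assumed baseline distributions, sham change and slope, and on applying the week-8 effect of 0.58 mg/dL and SD of 1.15; they apply to one visit at a time. The dependence of response on baseline in step 2 needs only the SD of 1.15, approximate normality and no mean change.

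The planned test keeps its level, the boundary value at 7.0 is a minor matter of interpretation, and the primary analysis and sample size are untouched. For SUA ≤ 6.0 the planned test is a reasonable choice.

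**What to change.** Before unblinding, amend the statistical section as follows.

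- **SUA ≤ 7.0 mg/dL:** logistic regression with group, baseline SUA and centre; report the standardised (marginal) risk difference with its 95% confidence interval beside the odds ratio.
- **SUA ≤ 6.0 mg/dL:** keep the chi-square or Fisher test as the main test; label any adjusted estimate as supportive only.
- **Boundary at 7.0 mg/dL:** no change is needed for the comparison to be valid; when reporting, show how many patients in each arm were already at or below 7.0 at week 0.

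No new data are needed, since baseline SUA and centre are already in the primary model. The cost is a change of wording and slightly more analysis work. The downside is that the odds ratio is conditional on the covariates and cannot be compared directly with the raw percentages, so the standardised risk difference must be shown with it.

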#### Patient and public involvement

Patients will not be involved in the design, conduct, or reporting of this study. The results of the study will be disseminated via a research article in a peer-reviewed journal. The results will also be disseminated at scientific meetings. Patients will also be informed of the results by follow-up staff at the research centers once the trial has finished.

## Discussion

Historically, hyperuricemia was considered of little clinical importance in the absence of gout or kidney stones. Yet over the past 20 years, increasing evidence has suggested that sustained elevation of serum urate levels can result in the supersaturation of body tissues with urate, leading to the deposition of sodium urate crystals in and around joints (1, 42, 43). As such, patients with hyperuricemia who have not yet developed gout symptoms may also experience joint damage. Therefore, early effective therapy is the key to preventing the onset of joint damage and other complications. However, whether or not, and when, conventional ULT drugs should be recommended to patients with asymptomatic hyperuricemia is still controversial. Some patients do not respond well to urate-lowering drugs, or cannot tolerate the adverse effects of the drugs. These limitations can lead to low adherence and disease aggravation. In this prospective trial, we aim to evaluate the efficacy and safety of acupuncture for the treatment of asymptomatic hyperuricemia by analyzing SUA outcomes.

This trial was designed to meet the methodological requirements of adequate power, allocation concealment, and necessary blinding, as outlined by the Good Clinical Practice guidelines (44). In the verum acupuncture group, manual acupuncture will be performed by licensed traditional Chinese acupuncturists. This is a form of traditional acupuncture therapy that has been used to treat various diseases in China and has been practiced for more than 2,000 years. After acupuncture needles are inserted into specific acupoints, standard manual manipulation of the needles generates de qi sensations, which play a key role in the specific effect of acupuncture (45). We will evaluate the dynamic changes in SUA levels of 180 eligible participants over a relatively long follow-up period (12 weeks). If acupuncture can reduce patients’ SUA levels to an optimal range and its clinical benefits are still reported at least 12 weeks after treatment is ended, this will compensate for the low persistence of effects from conventional urate-lowering therapy.

In acupuncture clinical studies, blinding and control treatments are always a challenge. An appropriate placebo acupuncture should be both physiologically ineffective and indistinguishable from true acupuncture. To observe the specific effects of acupuncture on asymptomatic hyperuricemia, we will use non-invasive placebo needles in the sham acupuncture group and the same acupuncture ritual will be performed in both groups, as described in our previous study (39).

It is accepted that uric acid can be affected not only by lifestyle factors (such as a high-purine diet, high alcohol intake, and a lack of exercise), but also by obesity, diabetes, comorbidities, and medications (46). Thus, it is crucial to consider the influence of these confounding factors when conducting acupuncture trials on an asymptomatic hyperuricemia population. In order to control the influence of lifestyle on uric acid, we will provide lifestyle-related guidance for hyperuricemia to all participants from baseline to the end of the follow-up period. All participants will receive the same recommendations using standardized written lifestyle guidance or by attending a monthly lecture. For improved adherence to the lifestyle prescription, all participants will be requested to record a lifestyle-related questionnaire and submit it to research assistants every 4 weeks (**see**
**Additional file 3**). Moreover, we also considered the influence of age, obesity, comorbidities, and medications on uric acid through strict inclusion and exclusion criteria.

The study does, however, have limitations. First, acupuncturists cannot be blinded, owing to the nature of acupuncture. As such, we cannot completely avoid an influence on study outcomes from the subjective behavior of the acupuncturists. Acupuncturists will perform the same treatment procedure in both groups, which may partially compensate for the lack of blinding in the acupuncturists. Second, sex differences are not included in the randomization adjustment factors, although evidence suggests that sex can influence serum uric acid levels (46). Third, the duration of this study may not be long enough to demonstrate a long-lasting effect from acupuncture, although we will observe whether the treatment effect from acupuncture can persist until 12 weeks after treatment.

At the time of submission of this protocol, participant enrollment is progressing well and data collection is well underway. Participant recruitment started on 13 July 2022 and is expected to end on 30 December 2024. We expect this study will provide reliable evidence regarding the efficacy and safety of acupuncture for asymptomatic hyperuricemia. If so, acupuncture can be recommended as an effective alternative treatment for patients with asymptomatic hyperuricemia when lifestyle changes have failed or patients meet the contraindications for urate-lowering drugs.

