### Data collection and management

#### Data collection

The investigator will conduct a baseline assessment within 1 month of obtaining informed consent. Demographic and epidemiological data will be obtained using a general information questionnaire, which will record information on age, gender, nationality, education, occupation, weight, height, previous disease history, routine physical examination, and medicine used for hyperuricemia. After receiving health education on hyperuricemia and 1 month of a low-purine diet, the serum uric acid concentrations of patients who have been enrolled in this study will be confirmed by laboratory tests.

During the treatment period, all patients will be asked to rate their acupuncture de qi sensations using the MASS immediately after the end of each acupuncture session. AEs related to acupuncture will be observed by acupuncturists. AEs, such as bent needles, stuck needles, broken needles, fainting, and infections, will be recorded. Serum uric acid concentrations will be tested at 4 and 8 weeks after randomization. During the follow-up period, serum uric acid concentrations will be tested at 12, 16, and 20 weeks after randomization. If patients have gout attacks after randomization, the time and location of the gout attack, and any medication used, will be recorded. All paper-based data will be recorded in the case report form (CRF). The data will be collected up to the time of withdrawal and will be included in the analysis unless participants specifically request for their data to be withdrawn.

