#### Sample size

The primary efficacy end point of this trial is the reduction in SUA from baseline at 8 weeks after randomization. The sample size of this study is driven by the superiority test of the primary efficacy endpoint, aiming to demonstrate a greater reduction in SUA concentration in the verum acupuncture group compared to the sham acupuncture group. Based on the pilot study and a previous clinical trial (33), we anticipate that SUA concentration will be reduced by an average of 0.58 mg/dL ± 1.15 mg/dL more in the verum acupuncture group than in the sham acupuncture group. Therefore, a sample size of 142 participants (71 patients in each group) is required to detect the difference between study groups with 85% power at an alpha level of 0.025 (one-sided). Considering an expected attrition rate of 20%, we plan to enroll at least 180 participants into this study.

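### Minor, near-free improvement: sex is said to influence serum uric acid and is recorded at baseline, but the primary ANCOVA does not adjust for it

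*Protocol article*

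**What the plan says.** All references are to the protocol article.

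- **Discussion (limitations):** "sex differences are not included in the randomization adjustment factors, although evidence suggests that sex can influence serum uric acid levels".
- **Randomization and blinding:** "participants will be randomly allocated to either the verum acupuncture or sham acupuncture group in a 1:1 ratio". The only stratification factor is study centre, with blocks of four.
- **Inclusion criteria:** both sexes are eligible, through the same SUA window of 7 to 11 mg/dL.
- **Data collection:** the baseline questionnaire is one "which will record information on age, gender, nationality, education, occupation, weight, height", so sex is on file for every patient.
- **Statistical analysis:** the primary endpoint is tested by ANCOVA "with the intervention group as the main effect and baseline SUA and study center as covariables". Sex is not in the model, and the article mentions no sex-adjusted or sex-specific analysis.

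**The concern.** The Discussion considers what else can move uric acid and says how most of it is handled: lifestyle by guidance given to everyone; age, obesity, comorbidities and medications by the eligibility criteria. Sex is also named as an influence, but it is controlled in none of the three usual places: eligibility, stratification or the model. The limitation mentions only randomisation and does not note that the analysis could adjust for sex with data already collected.

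If the arms differ by chance in their share of men, and sex predicts week-8 SUA beyond baseline SUA, part of that difference enters the treatment estimate. Adjustment removes it and reduces the residual variance. Adjustment chosen only after an imbalance has been seen would be post hoc and open to dispute, on a factor that the protocol itself had flagged.

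**Working it through.** **Inputs from the documents (Sample size):** the expected reduction is "an average of 0.58 mg/dL ± 1.15 mg/dL more in the verum acupuncture group than in the sham acupuncture group", at 85% power and one-sided alpha 0.025. The text states that "a sample size of 142 participants (71 patients in each group) is required", and continues: "Considering an expected attrition rate of 20%, we plan to enroll at least 180 participants".

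**Assumed inputs, because the documents give none:** share of men p from 50% to 90%; sex difference g in SUA change from 0.1 to 0.5 mg/dL, read as what remains after baseline adjustment; share R² of residual variance explained by sex, up to 5% (10% shown for reference). The planning SD of 1.15 mg/dL is taken as the residual SD of the model without sex.

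**1. The plan's own figure.** n per arm = 2 × (1.15/0.58)² × (1.960 + 1.036)² = 70.6, rounded up to 71, so 142 in total. Power at 71 per arm is 85.2% (84.7% with the noncentral t). With 20% attrition, 142/0.8 = 177.5, so 178 are needed and 180 is enough. The sample size stands without sex in the model.

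**2. Standard error.** 1.15 × √(2/71) = 0.193 mg/dL.

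**3. Chance imbalance.** The SD of the between-arm difference in the share of men is √(2p(1−p)/71). The 95% limit is 1.96 times that, and the shift in the estimate is the limit times g.

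| Share of men (assumed) | SD | 95% limit | Shift, g = 0.1 | Shift, g = 0.5 |
|---|---|---|---|---|
| 50% | 0.084 | 0.164 | 0.016 | 0.082 |
| 70% | 0.077 | 0.151 | 0.015 | 0.075 |
| 80% | 0.067 | 0.132 | 0.013 | 0.066 |
| 90% | 0.050 | 0.099 | 0.010 | 0.049 |

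The shift at the 95% limit is thus about 0.01 to 0.08 mg/dL. The largest value is 0.082/0.58 = 14% of the target effect and 0.082/0.193 = 0.42 standard errors. A one-SD imbalance gives about half of each shift.

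**4. Precision.** With sex in the model the residual SD becomes 1.15 × √(1−R²).

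| R² of sex (assumed) | Residual SD | Power at 71 per arm | Total N for 85% power |
|---|---|---|---|
| 0% | 1.150 | 85.2% | 142 |
| 1% | 1.144 | 85.6% | 140 |
| 2% | 1.138 | 85.9% | 140 |
| 5% | 1.121 | 86.9% | 136 |
| 10% | 1.091 | 88.6% | 128 |

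The two sets of assumptions agree: R² = g²p(1−p)/1.15² runs from 0.0007 (g = 0.1, 90% men) to 0.047 (g = 0.5, 50% men), so the 0–5% rows cover the range in step 3.

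**5. Simulation.** 20,000 runs per setting, 71 per arm, 80% men, total SD 1.15, no other covariates.

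| Sex difference g | Type I error without sex | with sex | Power without sex | with sex |
|---|---|---|---|---|
| 0.3 | 0.0252 | 0.0242 | 84.5% | 84.7% |
| 0.5 | 0.0250 | 0.0254 | 84.5% | 85.4% |
| 1.0 | 0.0261 | 0.0250 | 84.6% | 88.6% |

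The simulation standard error of the type I error is √(0.025 × 0.975/20,000) = 0.0011, so all six values are compatible with 0.025. The row for g = 1.0 lies outside the assumed range and is there only to show the trend.

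**The case against.** **The model is conventional and valid.** It contains treatment, the baseline value and the one stratification factor. Leaving out a further predictor causes no bias in expectation and no excess type I error, and chance imbalance is already part of the stated standard error. This stands. It describes the average over all randomisations, however. In the one trial actually run, an imbalance may be visible: with 80% men and g = 0.5 (both assumed), an imbalance at the 95% limit in favour of verum shifts the estimate by 0.066/0.193 = 0.34 standard errors, and the one-sided error given that imbalance is about 0.05. That is an argument for prespecifying adjustment, not evidence of a fault.

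**The cited evidence concerns SUA levels, while the endpoint is change, with baseline SUA in the model.** This largely stands. The documents do not show that sex predicts change beyond baseline. Baseline need not absorb everything: if the sexes have different underlying means but enter through the same window, they regress towards different means. The remaining difference is about (1−ρ) times the difference in means, with ρ the correlation between baseline and week-8 SUA. Assuming a 1.0 mg/dL difference in means and ρ of 0.5–0.8, that is 0.2–0.5 mg/dL.

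**The effect is trivial and rests on assumed inputs.** It is small, and the inputs are assumed; hence the ranges.

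**Further covariates may be in the full protocol or the SAP.** Neither is shown, and a sex-adjusted supplementary analysis may exist there. The point is therefore limited to the covariate set that the article itself states.

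**Stronger readings that the documents do not support.** A reader might infer that randomisation leaves sex unbalanced; it is unstratified, but allocation balances it in expectation. A reader might infer that the sample size or the alpha is wrong; the first reproduces and the second holds. A reader might infer that adjustment can only help; if sex does not predict the outcome beyond baseline, it costs a degree of freedom and gains nothing. Nor does the article call the limitation unavoidable.

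**Conclusion.** This is a minor improvement, not an error or a contradiction. The protocol flags sex as an influence on the variable it measures, collects it, and leaves it out of a primary model whose covariates it lists. What is lost is some precision and some protection against chance imbalance: a shift of about 0.01–0.08 mg/dL at the 95% limit (target 0.58, standard error about 0.19), and about 0–2 points of power if sex explains up to 5% of the residual variance. These sizes rest on assumed shares of men and an assumed sex effect. The facts about stratification, data collection and the model come from the article.

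**What to change.** In Statistical analysis, add sex as a prespecified covariate to the primary ANCOVA beside baseline SUA and centre, and fix this before unblinding. Name the model without sex as a sensitivity analysis.

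In the Discussion, keep the limitation, since it remains true that randomisation was not stratified by sex, and add that the primary analysis adjusts for it.

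The change is confined to the primary model. The other continuous endpoints are planned as t-tests or Mann–Whitney tests without covariates, so bringing sex in there would mean replacing the tests, which is a separate decision.

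Cost: one degree of freedom, no new data, and a minor protocol amendment, which under Monitoring and quality control goes back to the ethics committee. If sex does not predict week-8 SUA beyond baseline, nothing is gained.
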